**Fig. 2 Fig2:**
[figure not shown]
Study flow diagram

## Innovation

Reform rhetoric is common, but there are few rigorous, prospective studies examining implementation mechanisms and their relationship with behavioral health implementation outcomes in CJ settings. The national Stepping Up Initiative, which seeks to change the interface between behavioral health services and the justice system provides a large natural experiment and a unique research opportunity.

The proposed project also has novel implications for implementation science. Most implementation change process studies have been conducted within a single organization (e.g., health). There is limited understanding of implementation mechanisms that occur within or across systems with multiple goals, where some goals may be secondary or foreign [17]. This study will inform other implementation efforts by identifying the potential target mechanisms in complex, multi-agency systems [16].

## Methods

County matching and baseline covariate controls increase the rigor for this longitudinal natural experiment, which is described consistent with STROBE guidelines [25] (see Supplemental Materials). The study will measure target mechanisms and key outcomes in 475 Stepping Up counties and 475 matched counties at three waves: study baseline, 18 months, and 36 months. Since counties self-select to be in Stepping Up, we cannot randomize counties to the Stepping Up Initiative. Instead, we use a case-matched design using the Centers for Disease Control and Prevention (CDC) peer counties methodology to identify non-Stepping Up comparison counties with similar size, demographics, and health, economic, and justice indicators [26–28]. Stepping Up began in 2015 and has been registering counties over time. Therefore, at study baseline, the 475 Stepping Up counties had been participating in Stepping Up from 1 to 5 years. Wave 1 (i.e., baseline) values and months since each county began Stepping Up will serve as covariates. Therefore, analyses examine differences between groups in within-county rates of change between study waves controlling for Wave 1. Our quantitative survey results will be augmented with qualitative interviews with 60 counties at each wave to enrich our understanding of how the implementation mechanisms work.

### The Stepping Up Initiative

The goal of Stepping Up is to reduce the number of individuals with mental illness in jails and to improve access to community mental health services for currently or potentially justice-involved individuals. To join Stepping Up [14], counties pass a resolution to address behavioral health disorders (i.e., reduce unnecessary use of jail, increase access to behavioral health services) using a broad, locally adaptable six-step action plan: (1) convene a diverse team of leaders, (2) collect and review data on individuals in the justice system, (3) examine treatment and service capacity, (4) develop a plan with measurable outcomes, (5) implement the plan, and (6) track ongoing progress with data. Table 1 illustrates how we mapped Stepping Up’s six steps onto hypothesized CJ-IIM mechanisms. Stepping Up is a manualized approach, and the national initiative has offered a variety of written and other technical assistance resources.

Stepping Up outlines steps to help counties become more data-driven. Leaders of agencies within each county are asked to agree upon a mutual definition of terms such as “mental illness”, “connection to community-based care”, and “recidivism”. Stepping Up then encourages counties to identify and use a universal, validated mental health screening instrument for new intakes into the jail and other agencies. The screening tool identifies individuals in need of a full clinical assessment. Stepping Up offers toolkits to help counties examine how to capture screening and assessment results electronically and engage in information-sharing agreements. Counties are encouraged to track data on four key measures to assess impact of their efforts over time: (1) number of people with mental illnesses who are booked into jail, (2) average length of stay, (3) percentage of people connected to community-based treatment after release from jail, and (4) rate of return to jail. With this data infrastructure in place, counties can assess the effects of their efforts to address patient needs (e.g., substance use, mental illness, family discord), continuity of care, and reach of services. As Stepping Up counties work to iteratively improve services, they can track progress, focus county leaders on key outcome measures, and make the budgetary and programmatic case for needed resources. This study will assess counties’ progress on these steps.

### Survey methods

#### Stepping Up counties

When this project was submitted for funding, there were 475 counties designated as Stepping Up counties. Although new counties continue to join Stepping Up, for feasibility, this study will assess the 475 counties originally proposed.

#### Comparison counties

A peer group of 475 matched comparison counties was created using a county grouping methodology developed by CDC [26–28] and updated by our team [29]. Matching variables were drawn from three primary data sources: (1) Vera Institute’s incarceration trends database [30] for county pretrial and jail populations; (2) County Health Rankings & Roadmaps [31] for health, economic, social, and demographic information; and (3) the Uniform Crime Report [32, 33] for crime and police data.

Counties were nested within states and clustered on health and social indicators. Therefore, a hierarchical matching approach needed to be developed to accommodate state- and county-level covariates. The study principal investigators initially chose 34 of the most potentially relevant variables from the datasets based on expert knowledge. These variables included demographic factors (e.g., median household income, unemployment, total population, high school graduation rate, percent African American, percent Hispanic), inequality indicators (e.g., income inequality, residential segregation), health factors (e.g., poor mental health days, poor physical health days, HIV incidence), healthcare (e.g., mental health providers per capita, primary care physicians per capita, percent of drug treatment paid by Medicaid), crime, and criminal justice (e.g., per capita numbers of police officers, jail population, jail pretrial population, juvenile criminal cases). Based on random forest models and team feedback, these variables were reduced to 29 total variables: 22 predictors and 7 variables reflecting jail populations and mental health providers in the area (factors central to Stepping Up activities). Third, shrinkage-based variable selection techniques were applied to select variables that best predicted jail population per capita, pretrial population per capita, and per capita rate of mental health providers, without collinearity. Next, logistic models (which included both predictors and dependent variables in the previous models) were fitted to define variable weights and estimate the likelihood of each county classifying as a Stepping Up or non-Stepping Up county. Using these weights, matching scores were calculated for each county and used in an algorithm to find the best control matched county for each Stepping Up county among potential comparison counties within the same state.

The final variables used for county-matching scores included per capita rates of mental health providers, daily jail population, daily jail pretrial population, primary care providers, police, licensed psychologists, and community mental health centers. Final variables also included average number of physically unhealthy days (of 30), high school graduation, and income inequality rates, total county healthcare expenses, percent African American population, percent Hispanic population, percent drug treatment paid by Medicaid, county population, and an indicator reflecting presence of a medical school in the county. In states where the number of Stepping Up counties was higher than the number of potential comparison counties, state location, Medicaid expansion status, and justice/mental health policy were used to pair comparable states and then algorithmically match at the county level. If a county from the comparison group joins Stepping Up during the first year of the study, we find a new matching county. If this occurs after the first year of the study, the pair will be removed from analyses.

#### Survey respondents

The overall sample is 475 Stepping Up counties and 475 comparison counties. In each county, we will survey the administrators of community mental health, jail, probation, and community substance use treatment agencies (i.e., up to 4 respondents per county and ~ 3800 total; see Table 2). These respondents were selected because the jail and probation systems have the majority of individuals under justice control in a county, and mental health and substance use treatment administrators are responsible for the provision of behavioral health services for justice-involved individuals in the community.

**Table 2 Tab2:** Targeted type and number of survey respondents

Respondent type	Estimated number
Community mental health administrators	950
Jail administrators	950
Probation administrators	950
Community substance use treatment administrators	950

Note: The total survey population may be less than 3800 because some counties have the same person filling multiple roles listed above

To compile the respondent list, the research team developed a database of all Stepping Up and matched comparison counties. NACO-CSG-APAF provided a list of county contacts for Stepping Up counties. We contacted these individuals to provide the appropriate contact information for jail, probation, mental health, and substance use administrators in their county. We also conducted web-based searching. For comparison counties, we identified county-level experts through web-based searching. When contact information was not publicly available, we called individual agencies to identify the correct respondents. We also engaged in a snowball technique, in which we contacted experts already identified for assistance in identifying other possible respondents in their county.

#### Survey administration

The web-based survey is administered using Qualtrics. Using a procedure described by Dillman [34], respondents receive an introductory email that includes a NACO-CSG-APAF endorsement letter of support as well as key information to collect prior to beginning the survey (e.g., budget and staffing data). One week following administration of the introductory email, an invitation to participate in the survey is sent using Qualtrics. The research team sends follow-up emails once a week for 3 weeks following the initial invite with a reminder to participate. If the survey is not completed by the end of week 4, research team members make follow-up phone calls. During these calls, the research team provides multiple options for the respondents to complete the survey, including completion of the survey via telephone and receipt of a paper copy. Following the phone call, the research team continues to follow-up with respondents biweekly. Given the current context (i.e., COVID-19), we anticipate encouraging survey participation for 6 months before closing the survey. We will also provide county-specific feedback reports on county-level CJ behavioral health indicators as an incentive for study participation.

#### Survey validation

We use existing, validated measures where possible. When we needed to tailor items to CJ or to mental health, we used Cook [35] strategies for item development by testing new items using cognitive interviews [36]. Interviews covered question comprehension, decision processes, and response options.

Ten cognitive interviews were conducted in May 2020 with volunteers from Stepping up counties representing jail, probation/parole, community mental health, and community substance use treatment. Interviews were conducted via videoconference. Team members met to iteratively review interview results and revise the survey. At these meetings, each interviewer presented the responses and reflections from their interviews. Volunteer comments and interviewer/notetaker feedback, along with expert review by team members, were used to revise the survey. Changes were made to simplify and clarify survey questions and to remove redundancies. The amended survey was again reviewed by all team members.

### Measures

Measures will be collected at all 3 time points (see Table 3). All respondents will receive the same assessments. We refer to measures as “agency-level measures” when analyses of these measures will account for nesting within counties, but the primary focus is on agencies. We refer to measures as “agencies nested within counties” when we used nested analyses and our primary focus is on the county level. We refer to measures as “county-level” measures if they produce a single value for the county to be analyzed at the county level.

**Table 3 Tab3:** Study assessments

Construct	Measures and indicators	Time point		
		Baseline	8 months	36 months
**Target implementation mechanisms**				
Use of/capacity for performance monitoring	Performance Monitoring measure (primary) Adapted Routine Decision-Making scale [37]	X X	X X	X X
Use and functioning of nteragency teams	Adapted NCJTP Relationship Assessment Inventory [38]	X	X	X
Common goals and mission across agencies	Adapted NCJTP Goals/Mission scale [38] (primary) Agreement (kappa) among respondents within counties on ratings of the importance of providing mental health treatment services for justice-involved individuals	X X	X X	X X
System integration (vs. single programs)	Use of same screening/assessment instruments across agencies in the county	X	X	X
	Total score of 18+ on the NCJTP Relationship Assessment Inventory [38]	X	X	X
**Implementation outcomes**				
Number of justice-involved clients who received behavioral health services (primary)	How many justice-involved individuals received any mental health service and how many received any substance use service in the agency in the past year	X	X	X
Number of behavioral health EBPP available	Questions asking whether each listed EBPP is available to justice-involved individuals in the county	X	X	X
Resources for behavioral health EBPP	Funding increases and decreases Staff numbers, roles, training NCJTPS’s Assess Your Resources scale [38]	X X X	X X X	X X X
**Covariates**				
Baseline values of dependent variables	As assessed above	X		
Months since county joined Stepping Up	Self-report and Stepping Up records	X		
Matching score	Matching score used to choose matched comparison counties	X		
Indicators of whether the county shares (a) their mental health administrator, and/or (b) justice administrators with other counties	Questions asking whether the county shares (a) their mental health administrator, and/or (b) justice administrators with other counties	X		
**Descriptors and moderators**				
Type of agency	NCJTP About Your Organization scale [38]	X	X	X
Staffing (type, number, urnover)	Adapted NCJTP Staffing scales [38]	X	X	X
Organizational support for innovation	Adapted NCJTP Assess Your Organizational Culture scale [38]	X	X	X
Policy context	State mental health diversion funding, legislative reforms	X	X	X

#### Descriptors, predictors, and moderators (agency level)

A series of measures will be used to describe the inner context of each agency. *Type of agency* will be characterized using the National Criminal Justice Treatment Practices (NCJTP) survey About Your Organization scale [38]. *Staffing*, including type, number, and turnover, will be measured using the adapted NCJTP Staffing scales [38]. *Organizational Culture Support for Innovations* (a proposed moderator) will be assessed using an adapted version of the NCJTP Assess Your Organizational Culture scale [38].

#### Aim 1: Target mechanisms

##### Use of and capacity for performance monitoring (agencies nested within counties)

We created a Performance Monitoring measure which provides one point for each of the following: (1) whether counties are *able* to measure the 4 Stepping Up core metrics (number of mentally ill people who are booked into jail, average length of jail stay, percent who are connected to community-based treatment upon release from jail, and rate of return to jail) (up to 4 points); (2) each metric they regularly report (up to 4 points); and (3) each metric used for ongoing decision making (up to 4 points) (up to 12 points total). A secondary measure to capture performance monitoring identifies 7 kinds of decisions (e.g., budget preparation, medicine supply) and asks whether they were guided by each of the 4 Stepping Up core metrics (0 = no, 1 = yes), for up to 28 points possible. This measure was adapted from the Routine Decision-Making scale of the Performance of Routine Information System Management (PRISM) Toolkit [37].

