### Use of and capacity for performance monitoring

Performance monitoring refers to the use of data to assess population needs, understand how systems work, identify desired outcomes, and monitor progress. Stepping Up recommends that counties develop capacity for ongoing monitoring of four measures: (1) number of people with mental illnesses who are booked into jail, (2) average length of stay in jail, (3) percent linked to community-based treatment after release from jail; and (4) return to jail rate (i.e., recidivism). Doing so often requires infrastructure development since justice and behavioral health agencies lack common identifiers to track clients across systems, and few jurisdictions have electronic health record systems. This study will assess whether Stepping Up efforts improve counties’ ability to track and use performance monitoring metrics (mechanism) relative to comparison counties, and whether doing so improves implementation outcomes.

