### Power analyses

The expected sample (475 paired counties, up to 4 respondents per county, resulting sample size of ~ 3800) and the response rate of 50% gives an expected sample of 1900 respondents. Given that anywhere from 0 to 4 respondents may complete the survey in any given county, with a 50% overall response rate, we anticipate that 712 counties will have at least one respondent who completes the survey. We used a conservative (higher than expected) intraclass correlation coefficient of 0.1 for addressing clustering of agencies within counties.

For county-level analysis, an effect size of 0.2, power of 0.8, confidence level of 95%, and statistical significance level of 0.05 were used to calculate the minimum sample size. Repeated measures analysis required a minimum total sample size of 304 counties. For logistic regression and other nonlinear predictive models, depending on the type and quantity of variables used in the model, the minimum total sample size required varied between 156 and 489 counties. With attrition, our calculations showed a power of 0.9 and more for most county-level analyses.

For agency-level analysis, a conservative agency-level effect size estimate (*d* = 0.1), a power of 0.8, confidence level of 95%, and significance level of 0.05 were used to calculate the minimum required sample size. Repeated measures analysis comparing respondents from Stepping Up and comparison counties resulted in a minimum sample size of 524 respondents. When comparing the response measures, measured at the agency level, over time, a minimum sample size of 1200 respondents is required. For predictive logistic regression and other nonlinear predictive models, the minimum sample size varied between 673 and 1100 respondents. Given the larger sample size of this study, our calculations showed a power higher than 0.9 for agency-level analyses.

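### The primary Performance Monitoring model pools four administrator roles' answers on mostly jail-based metrics, and its stated covariates include no agency type or agency-type-by-wave term

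*Protocol article*

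**What the plan says.** The section on the measure gives one point for each core metric that the county can measure, each it regularly reports and each it uses for ongoing decisions. Four metrics at three points each make 12. The metrics are "number of mentally ill people who are booked into jail, average length of jail stay", then "percent who are connected to community-based treatment upon release from jail, and rate of return to jail".

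Under Survey respondents, "we will survey the administrators of community mental health, jail, probation, and community substance use treatment agencies". Under Measures, "All respondents will receive the same assessments". The measure's heading begins "Use of and capacity for performance monitoring (agencies nested within counties", and Measures says this label applies "when we used nested analyses and our primary focus is on the county level". So the target is the county, while the data are individual agencies' answers.

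Aim 1a makes the slope difference in this score the primary test. General approaches lists five covariates for all analyses: the Wave 1 value, months since joining, the matching score and two indicators of shared administrators. Agency type is not among them. Table 3 shows agency type collected at all three waves, and Aim 2 names it as a moderator for the client-count outcome only.

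For another county fact asked of all four roles, whether an evidence-based practice is available, the article sets a combination rule: one positive answer suffices. The Performance Monitoring score has no such rule for discordant answers.

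**The concern.** Bookings, length of stay and return to jail account for 9 of the 12 points, and the jail is the natural holder of those data. The Background says "justice and behavioral health agencies lack common identifiers to track clients across systems", which makes it plausible that some non-jail administrators see these metrics less clearly. If so, a real gain in a county's data capacity would show in the jail's answer and be averaged with up to three answers that move less. A null Aim 1a result could then mean either that nothing improved or that most respondents could not see the improvement. The same score family is the primary mediator in Aim 1b.

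Separately, about half of those surveyed are expected to respond. If the roles that respond change between waves, or change differently in the two groups, a model without role terms can take part of that change as a change in the score.

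**Working it through.** **Planning figures.** Expected respondents: 3800 × 0.5 = 1900, as stated. Counties with at least one respondent: the stated 712 equals 950 × (1 − 0.5²) = 712.5. Four independent respondents at 50% would give 950 × (1 − 0.5⁴) = 891, so both values are carried below.

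The stated minimum of 524 respondents is nearly recovered (526) by a repeated-measures between-group test with f = 0.1, three waves and an assumed within-respondent correlation of 0.5. The noncentrality is N·f²·3/(1 + 2 × 0.5). Reading the stated d = 0.1 literally, as f = 0.05, gives 2096. That labelling question is separate from this point.

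**Attenuation.** Let c be the change seen in non-jail answers as a fraction of the change in jail answers. This is an assumption, because the documents give no value. With equal response by role the jail supplies one answer in four, so:

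pooled effect / jail effect = 0.25 + 0.75c

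If only the jail saw change in its 9 points and everyone saw change in the 3 linkage points, the fraction would be (9/12)(1/4) + (3/12) = 0.4375, the same as c = 0.25.

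**Power.** Normal approximation, two equal groups, two-sided 0.05. The design effect is 1 + (1900/712 − 1) × 0.1 = 1.167, so the pooled effective n is 1900/1.167 = 1628. Jail respondents alone number 950 × 0.5 = 475.

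| c | Pooled fraction | Pooled power, jail d = 0.2 | Pooled power, jail d = 0.3 |
|---|---|---|---|
| 0 | 25% | 0.17 | 0.33 |
| 0.25 | 44% | 0.42 | 0.75 |
| 0.5 | 62.5% | 0.71 | 0.97 |
| 1 | 100% | 0.98 | 1.00 |
| Jail only, n = 475 | n/a | 0.59 | 0.91 |

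**Break-even.** Pooling and a single jail informant have equal power when the pooled fraction is √(475/1628) = 0.54, whatever d is. Then c = (0.54 − 0.25)/0.75 = 0.39. With 891 counties the design effect is 1.113 and the effective n 1707, which gives √(475/1707) = 0.53 and c = 0.37. The conclusion barely depends on which county count is right.

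**Variance due to role.** For an assumed jail/non-jail gap of D points and a within-role SD s, the share is 0.1875D²/(0.1875D² + s²). With s of 3 and 2 it is 2-5% for D = 1, 16-30% for D = 3 and 43-63% for D = 6.

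**Role mix.** If the jail share of respondents in one group moves by δ between waves, that group's raw mean moves by D·δ. For D of 1 to 6 this is 0.01 to 0.06 points per percentage point. Wave 1 adjustment and repeated answers from the same respondent remove part of it.

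**The case against.** A reader might infer that the primary slope is in fact diluted and that much of the score reflects who is answering. The documents do not support either statement. They give no role-specific means, variances or responsiveness. The remark on common identifiers concerns linking client records, not what administrators know. Survey validation describes cognitive interviews with volunteers from all four kinds of agency. The section on the initiative describes shared definitions, screening beyond the jail and information-sharing agreements, so whether a probation or treatment agency reports or uses a metric may be real agency-level signal. A stable difference between roles does not itself change a within-respondent slope.

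A reader might also infer from the "conservative (higher than expected) intraclass correlation coefficient of 0.1" that the county mean is mostly noise: 2.67 × 0.1/(1 + 1.67 × 0.1) = 0.23 reliability. That figure is a general planning value for clustering, not an estimate for this score, so no reliability of the measure follows. Nor does a stated bias in the mediation result: Aim 1b plans structural equation models, which can allow for measurement error.

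These points stand, and they rule out replacing the primary score. It can also be said that role terms belong in the full analysis plan. That carries less weight here, because the article states a covariate list for all analyses and leaves out a variable it already collects at each wave. The list is not called exhaustive, so adding to it contradicts nothing.

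**Conclusion.** The concern holds as a gap in the stated model. Four roles answer identical items about county metrics, three of them jail statistics, and the pooled model has no stated term for role or role by wave. The consequence for the slope difference runs from none (c = 1) to a fourfold attenuation (c = 0). This assumes equal response by role and non-jail answers that move no more than the jail's and not against them. Nothing in the documents places the study within that range. Whether a jail-informant score would have more power depends on the same unknown, with break-even at about 54% of the jail effect retained in the pooled data. The case for change is therefore protection and interpretability at little cost, not a demonstrated loss of power.

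**What to change.** - Keep the pooled nested score as the Aim 1a primary outcome and group by wave as the primary contrast.
- Add agency type and agency type by wave to that model. State how a person who holds more than one role is coded, since the note to Table 2 says this occurs.
- In a supporting model, add group by wave by agency type and report role-specific slopes.
- Prespecify a sensitivity analysis that takes the bookings, length-of-stay and return-to-jail items from the jail administrator only. About 475 counties would contribute, so it aids interpretation and does not replace the primary test.
- Do not make a designated-informant score primary.

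All items and agency type are already collected. The cost is a few extra model terms, one extra analysis and a sentence or two of plan wording, best fixed before follow-up data are analysed.
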